**Figure 1 fig1:**
[figure not shown]
Workflow of the randomized controlled trial. This flowchart illustrates the recruitment, screening, and enrollment process for participants. aMIC, abbreviated Memory Inventory for the Chinese; OPD, outpatient department; SCD, subjective cognitive decline.

The intervention group will undergo structured memorization training through recitation of Chinese Classics for 6 months. The intervention will be delivered by trained research assistants in weekly 60-min sessions, supplemented by approximately 10 min of individual daily practice over the six-month period. The control group will not receive memorization training during this period. To ensure reproducibility, a detailed intervention manual has been developed specifying recitation materials, progression criteria, and instructor guidance. All instructors will complete a standardized training program prior to the commencement of the study, encompassing both the theoretical rationale for the intervention and practical delivery skills. Instructor competency will be formally assessed before authorization to deliver sessions. As this study is conducted at a single center — China Medical University Hospital — inter-center standardization is not applicable to the current protocol; however, the intervention manual will be designed to support multi-site replication in future trials.

Intervention fidelity will be monitored through the following method. Daily home practice will be tracked via automated logs within the mobile application, capturing login frequency, session duration, and task completion rates. Adherence will be operationally defined as completion of at least 80% of the designated training, including at a minimum of 80% of scheduled training sessions and the fulfillment of at least 80% of the assigned daily practice throughout the six-month duration. Participants falling below this threshold at any monthly review will be contacted by the research team to identify and address barriers to engagement.

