### Interventions

2.4

The memorization intervention consists of structured recitation of Chinese Classics for a minimum of 5 min per day. The selection of Chinese Classics will be determined collaboratively by the research team and participants. Various memorization strategies will be introduced, including intensive repetition techniques and visualization strategies. Participants may begin by reading the designated text aloud for at least 5 min daily before progressing to full memorization. The research team recommends beginning with the classical text “Di Zi Gui,” translated as Standards for Being a Good Student. To facilitate adherence and standardization, a mobile application currently under development will assist participants in memorization training, provide access to digital literature materials, and record daily recitation duration.

After six consecutive months of training, participants in the intervention group will undergo a standardized recitation assessment. The primary performance metric will be the number of correctly recited Chinese characters within a fixed time frame. For example, Di Zi Gui contains 1,080 Chinese characters. Participants will be required to recite the entire text within 11 min, with no more than eight omitted or incorrectly recited characters. Participants who meet these criteria will be classified as having passed the assessment. The recitation assessment will be conducted by qualified judges affiliated with the Bliss & Wisdom Foundation of Culture and Education, who are capable of reciting the complete text from memory. During evaluation, judges will reference the original text while participants perform their recitation to ensure objective scoring accuracy.

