##### Statistical analysis

2.5.2.5

Statistical analyses will be conducted within the framework of the general linear model (GLM). For the primary clinical outcomes (e.g., subjective cognitive measures, neuropsychological test scores), a linear mixed-effects model will be used to handle the repeated-measures structure of the data throughout baseline, post-intervention, and follow-ups, with time, group, and group × time interaction as fixed effects, and subject as a random effect. This approach naturally accommodates missing data under the missing-at-random (MAR) assumption without requiring complete cases. The primary analysis will follow the intention-to-treat principle, including all randomized participants regardless of adherence or dropout, with missing values handled using multiple imputation based on baseline characteristics and available follow-up data. A per-protocol sensitivity analysis will also be conducted, restricted to participants who complete at least 80% of the intervention sessions. Covariates to be included in adjusted models will comprise age, sex, years of education, and baseline cognitive scores, selected *a priori* for their known associations with cognitive outcomes in SCD populations.

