#### Data management and missing data

2.7.4

Data entry is performed by trained personnel with range checks to promote quality. Missing data will be handled using multiple imputation or the Last Observation Carried Forward method. Sensitivity analyses will be conducted to assess the robustness of the primary findings with respect to participant adherence levels.

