### Strengths and limitations

3.2

A major strength of this study lies in its focus on a Chinese-speaking population, which remains underrepresented in longitudinal cognitive training research. By integrating multimodal assessments and long-term follow-up, this study aims to provide novel insights into the trajectory of SCD and the potential disease-modifying effects of sustained cognitive training within this population.

Several limitations should be acknowledged. First, recruitment may be challenging, as individuals with SCD often present with mild symptoms and may not seek medical attention in outpatient settings. Second, the comprehensive pre- and post-intervention assessments are time-intensive and may reduce participant willingness and adherence. Third, participants may be aware of whether they are assigned to the intervention or control group because of the use of a non-active control group, which may introduce performance and expectancy biases. Additionally, the use of a mobile application for training may pose usability challenges for older adults, potentially contributing to dropout.

To mitigate these limitations, participants will be recruited from both Neurology and Psychiatry departments, as well as through collaborations with community activity centers to enhance outreach. To improve adherence, only individuals willing to complete study assessments will be enrolled, and the training platform will be optimized for elderly users (e.g., larger Chinese characters and simplified interface design). Adherence will be operationally delineated as the completion of no less than 80% of the designated intervention, specifically including attendance at a minimum of 80% of scheduled training sessions and the fulfillment of at least 80% of the assigned daily practice throughout the six-month duration. Adherence will be monitored continuously throughout the trial using automated session logs recorded in the mobile application, and any participant who falls below the threshold will be flagged for follow-up by the research team. Reasons for non-adherence and dropout will be systematically documented to inform the interpretation of findings and the design of future trials.

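### The per-protocol set is defined by session attendance alone, while the article's own adherence rule also requires 80% of the assigned daily practice

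*Protocol article*

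**What the plan says.** Section 2.5.2.5 (Statistical analysis) makes intention-to-treat the primary analysis and adds a per-protocol sensitivity analysis "restricted to participants who complete at least 80% of the intervention sessions". Daily practice is not part of that criterion.

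Section 2.1, in the text after Figure 1, gives the adherence rule: "Adherence will be operationally defined as completion of at least 80% of the designated training". It then names two components, 80% of the scheduled training sessions and "the fulfillment of at least 80% of the assigned daily practice throughout the six-month duration". Section 3.2 repeats both: "attendance at a minimum of 80% of scheduled training sessions and the fulfillment of at least 80% of the assigned daily practice".

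The dose appears in two places. Section 2.1 describes delivery "in weekly 60-min sessions, supplemented by approximately 10 min of individual daily practice over the six-month period". Section 2.4 describes "structured recitation of Chinese Classics for a minimum of 5 min per day". Neither place says which amount is the assigned one for the 80% rule.

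Section 2.7.4 plans further sensitivity analyses on the "robustness of the primary findings with respect to participant adherence levels", without giving a threshold.

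**The concern.** A per-protocol analysis is meant to show the effect in people who received the intervention as the protocol defines it. Here the protocol defines receipt by two components, and the per-protocol set checks only one. The component left out is a large part of the planned training: more than half of the minutes at 10 min per day.

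Two consequences follow. The per-protocol estimate could include people who did little or no home recitation, so it would not answer the question its name implies. And the per-protocol analysis and the adherence-level analyses of section 2.7.4 could describe different groups under similar 80% wording, which a reader of the results would have no reason to expect.

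**Working it through.** **The two rules side by side**

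| | Scheduled sessions | Daily practice |
|---|---|---|
| Adherence (sections 2.1 and 3.2) | at least 80% | at least 80% |
| Per-protocol set (section 2.5.2.5) | at least 80% | not required |

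Everyone who meets the two-part rule also meets the session rule, but not the reverse. The two-part set is therefore contained in the sessions-only set.

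**Inputs**
- Weekly 60-min sessions and about 10 min of daily practice: section 2.1.
- Minimum of 5 min per day: section 2.4.
- Six months taken as 26 weeks, or 182 days, with one session per week: assumption.

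**Planned minutes**
- Sessions: 26 × 60 = 1,560.
- Home practice: 182 × 10 = 1,820, or 182 × 5 = 910.
- Total: 1,560 + 1,820 = 3,380, or 1,560 + 910 = 2,470.
- Home share: 1,820/3,380 = 53.8%, or 910/2,470 = 36.8%.

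**Session threshold:** 0.8 × 26 = 20.8, so 21 sessions.

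**Share of planned minutes received**

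| Case | 10 min per day | 5 min per day |
|---|---|---|
| 21 sessions, no home practice | 1,260/3,380 = 37.3% | 1,260/2,470 = 51.0% |
| 26 sessions, no home practice | 1,560/3,380 = 46.2% | 1,560/2,470 = 63.2% |
| Two-part minimum: 21 sessions and 80% of home minutes | (1,260 + 1,456)/3,380 = 80.4% | (1,260 + 728)/2,470 = 80.5% |

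All three cases enter the per-protocol set, but only the third is adherent. Even full attendance cannot by itself bring a participant to 80% of the planned minutes.

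**How far the sets could differ in size (illustration only).** Take 30 in the intervention arm and assume that 80% meet the session rule, so the sessions-only set is 24.
- If 50% meet the daily rule, the two-part set lies between 30 × (0.8 + 0.5 − 1) = 9 and 30 × 0.5 = 15.
- If 80% meet the daily rule, it lies between 30 × (0.8 + 0.8 − 1) = 18 and 30 × 0.8 = 24.

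The article gives no expected adherence rates, so these figures show a range and are not a forecast.

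**Base for the daily-practice percentage.** If minutes are counted, a participant who practises exactly 5 min every day scores 910/1,820 = 50% on a 10 min base and 910/910 = 100% on a 5 min base.

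**The case against.** The strongest reply is that the two rules serve different purposes. Sections 2.1 and 3.2 define adherence for monitoring and follow-up; section 2.5.2.5 defines an analysis set, states its own clear criterion and does not call it adherence. A set based on attendance is a legitimate choice. That stands as far as it goes. But the article calls its two-part rule the operational definition of adherence and then uses the same 80% figure for per-protocol status, without saying that a different standard is meant. This is a conflict between two stated rules, so it is not a detail that can simply be left to a statistical analysis plan.

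It is also fair that the case with no home practice is extreme. Section 2.1 provides for contact with anyone below threshold at a monthly review, and section 2.7.2 adds monthly calls. These measures make the case less likely but do not remove the mismatch.

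Four stronger readings are tempting and not supported:
- *The daily amount is missing or contradictory.* Two amounts are given, and about 10 min and a minimum of 5 min can be read as a target and a floor. What is open is only which one the 80% refers to. The unit of counting may be settled in the intervention manual or the analysis plan. If completed tasks are counted, the difference in minutes need not matter.
- *Intervention sessions might include app sessions.* Section 3.2 does speak of "using automated session logs recorded in the mobile application", but both statements of the adherence rule list scheduled sessions and daily practice separately. The natural meaning is the weekly sessions.
- *The feasibility aim is undermined.* The adherence rule is stated twice and consistently. The per-protocol wording does not alter it.
- *The main result is at risk.* The primary analysis includes all randomized participants regardless of adherence.

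**Conclusion.** The concern holds as a minor inconsistency. The per-protocol set in section 2.5.2.5 admits participants whom sections 2.1 and 3.2 classify as non-adherent. At the boundary such a participant has received about 37% of the planned minutes at 10 min per day, or 51% at 5 min per day, against about 80% guaranteed by the two-part rule. These percentages rest on 26 weekly sessions and 182 days, and the second treats the stated floor as the planned dose.

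The reach is limited to the per-protocol analysis and to how it compares with the adherence-level analyses of section 2.7.4. How many participants would be reclassified cannot be known from the article, and no effect on any estimate is shown.

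**What to change.** In section 2.5.2.5, define the per-protocol set by the rule already in sections 2.1 and 3.2. For the intervention arm, for example: *participants who attended at least 80% of scheduled sessions and fulfilled at least 80% of assigned daily practice*. If the investigators also want the sessions-only set, keep it as a second analysis labelled as session attendance.

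As a minor addition, state in section 2.1 or 2.4 whether about 10 min or the 5 min minimum is the base for the 80% daily-practice rule. Which one applies is for the investigators to decide. It is best fixed before logging starts, while the app is still under development (section 2.4).

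The cost is a few words. The per-protocol set can only stay the same or shrink, so its estimate may be less precise. That is acceptable for a sensitivity analysis, and keeping the attendance set beside it would show how much depends on home practice.

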The study is designed as a randomized, assessor-blinded, controlled pilot study. A stratified block randomization sequence will be generated by an independent statistician using computer-generated random numbers, with stratification by age and sex to ensure balanced group allocation. Block sizes will be randomly varied to prevent predicting upcoming assignments. Allocation concealment will be ensured using the Sequentially Numbered, Opaque, Sealed Envelopes method; envelopes will be prepared and safeguarded by personnel not involved in recruitment, eligibility assessment, or intervention delivery. After eligibility assessment and informed consent are completed, a designated research assistant — otherwise uninvolved in outcome assessment — will open the envelope to reveal group assignment. Prior to allocation disclosure, all research personnel will remain blinded to the randomization sequence. Given that the intervention is behavioral in nature, complete blinding of participants and interventionists is not feasible. However, several measures will be implemented to minimize performance bias. Participants will be instructed not to discuss their group assignment with outcome assessors. Interventionists will have no role in outcome measurement or data analysis. Outcome assessors — including neuropsychological evaluators (psychologists) and radiologic technologists — will be formally blinded to group allocation throughout the trial and will be kept separate from the intervention team. To maintain blinding integrity, assessors will be reminded of their blinded status at each assessment visit, and any unblinding events will be documented and reported. Data analysts will similarly remain blinded to group assignment until the primary analysis is complete. The inherent risk of performance bias arising from participant awareness of group assignment will be mitigated by standardizing intervention protocols, using objective outcome measures where possible, and monitoring for differential dropout between groups.

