For the neuroimaging analyses, task-related regressors will be convolved with the canonical hemodynamic response function, and motion parameters will be included as nuisance covariates. A high-pass filter of 128 s will be applied to remove low-frequency drift. At the single-subject level, voxel-wise GLM analyses will be performed to identify task-related activation patterns. Contrasts of interest (e.g., recitation versus resting baseline) will be evaluated using directional T-contrasts. At the group level, individual contrast maps will be entered into second-level random-effects models. Directional two-sample T-tests will be used for between-group comparisons, and conditions with similar activation patterns may be combined to enhance statistical power. Statistical significance will be set at *p* < 0.05, corrected for multiple comparisons using the false discovery rate (FDR) at the voxel level. For exploratory analyses, an uncorrected threshold of *p* < 0.001 may be applied. Extracted effect sizes from predefined ROIs will be further analyzed using Statistical Product and Service Solutions (SPSS). One-way analysis of variance will be used to assess condition-related differences, while Spearman’s rank-order correlation will evaluate associations between neural activation and clinical variables (e.g., years of education and Cognitive Reserve Index questionnaire (CRI-q) scores). Statistical significance will be defined as *p* < 0.05.

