#### Gut microbiota profiling by full-length 16S rRNA gene sequencing

2.5.5

Full-length 16S rRNA gene sequencing will be performed using the PacBio Revio platform, enabling species-level taxonomic resolution for precise identification of microbial strains capable of producing neuroactive metabolites. PCR amplification will be conducted using universal primers 27F and 1492R, followed by SMRTbell library preparation and sequencing, yielding approximately 10,000 high-quality circular consensus sequencing (CCS) reads (Q30) per sample. Bioinformatic processing will be performed using QIIME2, with taxonomic classification based on the SILVA database. Downstream analyses will include alpha and beta diversity indices (e.g., Shannon index), taxonomic annotation, and differential abundance analysis between study groups using DESeq2. DNA extraction and library preparation procedures will follow those described by Tsai et al. (2025).

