### Statistical methods

2.6

The primary efficacy analysis will be conducted using generalized linear mixed-effects models to analyze repeated measures data, with adjustment for relevant covariates. Microbiome analyses will be performed using DESeq2 to identify differentially abundant taxa and linear discriminant analysis effect size to detect potential microbial biomarkers. Metabolomic data will be analyzed using partial least squares discriminant analysis, and pathway enrichment analysis will be conducted using the MetaboAnalyst platform. Multi-omics integration will be performed using Spearman correlation-based network analysis and causal mediation analysis to investigate regulatory mechanisms along the gut-brain axis. Multiple comparisons will be corrected using FDR, with a threshold of *q* < 0.05. All statistical analyses will be conducted using R (version 4.4.0; R Core Team, 2024) and SPSS (version 29.0; IBM Corp., Armonk, NY, USA), with statistical significance set at *p* < 0.05.

Given the inherent complexity and multi-layered nature of multi-omics data, if the aforementioned methods are insufficient for comprehensive analysis, we will collaborate with the institutional Artificial Intelligence Center affiliated in our hospital to implement advanced analytical approaches. These may include machine learning, network-based modeling, and partial least squares regression, among others, to construct predictive models that characterize causal or associative relationships between biological markers and clinical outcomes (e.g., cognitive function and depression). The predictive performance of different models will be systematically compared.

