Consistent with the hypothesis-generating nature of this pilot research, study outcomes are organized within a predefined inferential hierarchy. The primary outcome is designated as the principal efficacy endpoint and will serve as the main basis for evaluating intervention-related effects. The secondary outcome is pre-specified *a priori*; however, given the limited sample size typical of pilot studies, findings will be interpreted as supportive and hypothesis-generating rather than definitive. EEG, gut microbiota, and metabolomic measures are designated as exploratory outcomes. These measures are not powered for confirmatory inference and are intended primarily to generate preliminary effect-size estimates and identify candidate biomarkers for future adequately powered confirmatory trials.

Based on these findings, we anticipate that the primary outcome of this pilot trial is intervention-induced change in resting-state fMRI activation within the left medial temporal region, encompassing the hippocampus and parahippocampal gyrus, from baseline (T0) to post-intervention assessment at 6 months (T1). Increased resting-state fMRI activation in the left medial temporal region following recitation training is interpreted as reflecting enhanced cognitive reserve — the brain’s capacity to sustain normal cognitive function despite underlying neurodegenerative burden — consistent with the compensatory scaffolding framework of cognitive aging (Reuter-Lorenz and Park, 2014). We anticipate that the intervention group will demonstrate significantly greater increase in left medial temporal region activation compared to controls, with the effect expected to be more pronounced in participants with lower educational attainment — consistent with a compensatory neural response in individuals with lower a priori cognitive reserve (Stern et al., 2020).

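### Allocation is stratified by age and sex, but the only stated between-group imaging test has no age or sex term; to the extent that these predict the imaging outcome, it is conservative and its standard error too large

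*Protocol article*

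**What the plan says.** All references are to the protocol article.

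- **Allocation (section 2.1).** Stratified blocks of randomly varied size, "with stratification by age and sex to ensure balanced group allocation".
- **Clinical outcomes (section 2.5.2.5, first paragraph).** A linear mixed-effects model, followed by "Covariates to be included in adjusted models will comprise age, sex, years of education, and baseline cognitive scores". The reason given for these covariates is their association with cognitive outcomes.
- **Imaging (section 2.5.2.5, second paragraph).** At subject level, "motion parameters will be included as nuisance covariates". At group level, "individual contrast maps will be entered into second-level random-effects models", and then "Directional two-sample T-tests will be used for between-group comparisons". No age or sex term appears at either level.
- **Status of imaging.** Section 3.3 says that "the primary outcome of this pilot trial is intervention-induced change in resting-state fMRI activation within the left medial temporal region", and makes a task-based fronto-striatal change the secondary outcome. Section 2.5 calls functional MRI an exploratory mechanistic outcome.
- **General methods (section 2.6).** "The primary efficacy analysis will be conducted using generalized linear mixed-effects models to analyze repeated measures data, with adjustment for relevant covariates". Neither the outcome nor the covariates are named there.

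**The concern.** Balancing the arms on age and sex means that chance differences in these factors hardly contribute to the difference in means. The true sampling variance of that difference falls accordingly. A two-sample t-test estimates its error from the whole within-arm spread, which still contains the age and sex variation. The reported standard error then describes a less precise design than the one used. This holds even if the input is a change map, as long as change itself depends on age or sex.

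Two things are at stake. A between-group imaging comparison in about 60 people may give up power that is available at almost no cost. And the trial's stated aim is to supply effect estimates for a larger study, so intervals around those estimates should have the stated coverage. The imaging and clinical analyses would also treat the stratification factors differently, with no reason given.

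**Working it through.** **Plan's own figure.** The only computed sample size (section 2.3) is 383 per group for d = 0.18, one-tailed α = 0.05 and power 0.80, and it is offered for neuropsychological scores. The noncentral t distribution gives power 0.7997 at 382 per group and 0.8006 at 383, so the figure reproduces. It contains no stratification or covariate term and does not bear on this point.

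**Inputs from the article.** 60 participants, 30 per arm (section 2.3); stratification by age and sex with random block sizes (section 2.1); a directional test (section 2.5.2.5). One-sided α = 0.05 is taken from section 2.3.

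**Assumed, because the article gives no value.** R², the share of imaging-outcome variance explained by age and sex, from 0 to 0.30; two age classes crossed with sex; blocks of 2 and 4; an effect of d = 0.65, which has 80% power with 30 per arm when R² = 0.

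**Analytic step.** With total variance σ² and n per arm, the t-test reports a standard error near σ√(2/n). Under stratified allocation the true standard deviation of the difference is near σ√(1 − R²)·√(2/n). The ratio is k = 1/√(1 − R²). By the normal approximation, the one-sided 5% test rejects under the null with probability 1 − Φ(1.645k), and a nominal 95% interval covers with probability 2Φ(1.96k) − 1.

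| R² | k | 1.645k | Type I error | 1.96k | Coverage |
|---|---|---|---|---|---|
| 0 | 1.000 | 1.645 | 5.0% | 1.960 | 95.0% |
| 0.05 | 1.026 | 1.688 | 4.6% | 2.011 | 95.6% |
| 0.10 | 1.054 | 1.734 | 4.1% | 2.066 | 96.1% |
| 0.20 | 1.118 | 1.839 | 3.3% | 2.191 | 97.2% |
| 0.30 | 1.195 | 1.966 | 2.5% | 2.343 | 98.1% |

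**Simulation.** 10,000 trials per setting with 60 participants, comparing the t-test with a linear model on group, age class and sex.

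| R² | SE ratio, t-test / adjusted | Type I, t-test | Type I, adjusted | Power, t-test | Power, adjusted |
|---|---|---|---|---|---|
| 0 | 1.000 | 5.3% | 5.2% | 79.7% | 79.7% |
| 0.05 | 1.025 | 4.4% | 4.8% | 81.0% | 82.2% |
| 0.10 | 1.055 | 4.0% | 5.0% | 80.9% | 83.4% |
| 0.20 | 1.119 | 3.3% | 5.0% | 82.0% | 87.0% |
| 0.30 | 1.197 | 2.5% | 5.0% | 84.2% | 90.8% |

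A separate run (8,000 trials per setting, blocks of 2, 4 or 6) gave t-test type I errors of 4.9%, 4.7%, 4.0%, 3.3% and 2.5% for the same R² values. Power at d = 0.65, t-test against adjusted, was 80.7/80.7, 80.2/81.4, 80.6/82.7, 82.2/86.9 and 83.9/90.6%. Monte Carlo error on a 5% rate is √(0.05 × 0.95 / 10,000) = 0.22 points, or 0.24 with 8,000 trials. The departure from 5% at R² = 0.05 is therefore close to noise in a single run, though it agrees with the analytic value. From R² = 0.10 upwards it is clear.

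**The case against.** **The primary outcome may already have an adjusted model.** Section 2.6 promises a covariate-adjusted mixed model for the primary efficacy analysis, and section 3.3 calls a resting-state fMRI change primary. The imaging paragraph of section 2.5.2.5 is written mainly around task regressors and task contrasts. A reader might infer that the primary endpoint is certainly tested without age and sex; the documents do not support that. They leave open which model serves it. This stands, and is why the fix asks for that to be settled.

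**The omission may be only condensation.** Second-level models can carry covariates, and section 2.5.2.5 opens within the general linear model framework. But the text goes on to name a specific test whose standard form has no covariates, next to a covariate list given for the other outcomes. That is a stated choice and not a blank.

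**The effect may be negligible.** Nothing in the article links age or sex to the imaging outcome. The sample is restricted (60 or older, MoCA at least 26, limited white matter burden) and the outcomes are within-person changes, so the 20–30% rows may be too high. At 5–10% the loss is about 1 to 2 power points. This stands as a limit on size.

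**Other stronger readings fail.** The region-of-interest step names analysis of variance for condition differences and Spearman correlation, so it states no unadjusted arm comparison to replace. For microbiota, section 2.5.5 says only "differential abundance analysis between study groups using DESeq2"; a design formula is detail that an article may leave out, so no fault is claimed there. Nor would later sizing be misled by a biased estimate: the estimate is unbiased and the ordinary pooled standard deviation is the usual denominator of Cohen's d.

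**Conclusion.** The point holds, conditionally and for the imaging comparisons only. The sole stated between-group imaging test leaves out the stratification factors. If age and sex explain 5, 10, 20 or 30% of outcome variance, its standard error is about 3%, 5%, 12% or 20% too large, its one-sided type I error is about 4.5%, 4.0%, 3.3% or 2.5% in place of 5%, and it gives up about 1, 2, 5 or 7 power points at d = 0.65. If they explain nothing, nothing is lost. These figures rest on the assumed R² and strata and on a single univariate test; the voxel-wise, FDR-corrected analysis was not simulated.

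A reader might infer that the whole trial forfeits the benefit of its stratification. It does not: the clinical outcomes have an adjusted model, and the imaging point estimate keeps the balance gained. The t-test's own power even rises with R², from 79.7% to 84.2%. What fails is that the standard error, p-value and interval do not reflect this gain. There is no bias and no inflated type I error.

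**What to change.** 1. In the imaging paragraph of section 2.5.2.5, replace the two-sample t-test with a second-level general linear model containing group, age and sex, and test the group contrast.
2. State that any between-group comparison of extracted region-of-interest values includes the same terms.
3. Reconcile sections 2.5.2.5, 2.6 and 3.3: say whether the second-level imaging model or the covariate-adjusted mixed model serves the resting-state outcome that section 3.3 calls primary, and confirm that age and sex are in it.

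The cost is two residual degrees of freedom (58 to 56 with 60 participants), two columns in the planned SPM design and a few sentences. Age and sex are known for everyone at randomisation, so no extra data are needed.
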